### **1.5 ANGEL-ASPECT Trial design**

ANGEL-ASPECT trial is a PROBE study initiated by researchers to explore the effectiveness and safety of EVT in patients with anterior circulation large vessel occlusion with ASPECTS 3-5 or infarction core volume 70-100ml within 24 hours. ANGEL-ASPECT trial allows multiple imaging modalities to screen for LICV patients, but at the same time imposes certain limitations on the range of ASPECTS or infarct core volume. The main purpose was to reduce the risk of EVT while enrolling as many LICV patients as possible. The primary image inclusion criteria of ANGEL-ASPECT was NCCT-ASPECTS 3-5, and the infarct core volume 70 ml-100 ml was used as auxiliary inclusion criteria. Briefly, the inclusion criteria for LICV are: (1) If NCCT-ASPECTS is 3-5 and presentation is within 24 hours of onset, patients are enrolled without limitation of infarct core volume. (2) For NCCT-ASPECTS 0-2 and core infarction volume 70 ml-100 ml, patients are enrolled. (3) If NCCT-ASPECTS is >5 and between 6 to 24 hours from symptom onset, only patients with infarct core volume 70 ml-100 ml are enrolled.

Subgroup analysis will focus on age, LKW to randomization time, NIHSS score, IV thrombolysis, occlusion site, ASPECTS, infarct core volume, and stroke etiology.

ANGEL-ASPECT is the only randomized controlled trial conducted in China for LICV patients so far. The results of this trial will clarify whether EVT is effective and

safe in Chinese LICV patients.

## **2. Study objective**

### **2.1 Primary objective**

To estimate if acute ischemic stroke patients with anterior circulation LVO and large infarct core at 0-24 hours after stroke onset have improved neurological functional outcomes when treated with BMM plus EVT compared to BMM alone.

### **2.2 Secondary objective**

To estimate if acute ischemic stroke patients with anterior circulation LVO and large infarct core at 0-24 hours after stroke onset have increased the risk of sICH when treated with BMM plus EVT compared to BMM alone.

## **3. Study design**

### **3.1 Study design**

Multicenter, Prospective, Randomized, Open-label, Blinded End-point (PROBE) trial design (Figure 1).

[figure not shown]

**Figure 1. Study design: randomization algorithm**

### 3.2 Randomization

The random code will be generated by a central network randomization system with 24h real-time online service based on the simple randomization method. The researcher in each center will obtain the random code from the central network randomization system according to the enrollment order. Patients who meet the inclusion criteria and in whom written informed consent can be obtained, will be randomly assigned to the following treatment groups in a 1:1 ratio:

- BMM plus EVT group: patients will receive EVT with stent retriever or contact aspiration as first-line devices for thrombectomy plus BMM;
- BMM group: Patients will receive BMM alone.

### 3.3 Follow-up schedule

- (1) Face-to-face visit: day of randomization, 36 hours ( $\pm 12$  hours), 7 days ( $\pm 1$  day) /at discharge whichever is earlier
- (2) Telephone visit: 30 days ( $\pm 3$  days), 90 days ( $\pm 7$  days), and 12 months  $\pm 14$  days

### 3.4 Blind design

- (1) Only the patient and the treating physician are aware of the randomization

information, and the evaluation of information at baseline and in-hospital visits that relate to the study endpoints should be evaluated by an investigator who is not aware of the patient group assignment and the treatment received.

- (2) The primary endpoint visits are standardized visits conducted by trained third party personnel who are not aware of the patient's randomization assignment and their actual treatment status. All follow-up calls were recorded, and a follow-up report was formed.
- (3) All imaging data related to the study will be collected for central interpretation. The images at each visit site were interpreted independently by a core lab, and the readers were unaware of the patient's baseline information, treatment received (except EVT angiography images), and prognosis.

## **4. Participant selection**

### **4.1 Inclusion Criteria**

#### **4.1.1 Center Inclusion Criteria**

- (1) Equipped with an emergency department and neurology department for stroke patients
- (2) Equipped with a stroke team operating 24/7
- (3) Capable of endovascular therapy and IV thrombolysis for acute ischemic stroke patients

#### **4.1.2 Clinical Inclusion Criteria**

- (1) 18 to 80 years of age
- (2) Presenting with symptoms consistent with an acute ischemic stroke
- (3) Pre-stroke mRS score 0-1
- (4) NIHSS score 6-30 at the time of randomization
- (5) Randomization can be finished within 24 hours of stroke onset (stroke onset time is defined as last known well time)
- (6) Informed consent signed by the patient or legally authorized representative

### 4.1.3 Neuroimaging Inclusion Criteria

- (1) CTA or MRA proven occlusion of the Internal Carotid Artery (ICA) terminus or M1 segment of the Middle Cerebral Artery (MCA)
- (2) Imaging evidence of low ASPECTS (based on NCCT) or large infarct Core (defined as rCBF <30% on CT perfusion or ADC<620 on MRI) fulfill one of the following criteria:
  - 4) ASPECTS 3-5
  - 5) ASPECTS >5 (6h-24 h) with infarct core volume 70-100 ml
  - 6) ASPECTS <3 with infarct core volume 70-100 ml

## 4.2 Exclusion Criteria

### 4.2.1 Center Exclusion Criteria

- (1) Centers in which the number of acute ischemic stroke cases treated with endovascular procedures are less than 20
- (2) Centers that are unable to comply with the research protocol

### 4.2.2 Clinical Exclusion Criteria

- (1) Females who are pregnant, or those of childbearing potential with positive urine or serum beta Human Chorionic Gonadotropin test
- (2) Known severe allergy (more than a rash) to contrast media uncontrolled by medication
- (3) Refractory hypertension that is difficult to control by medication (defined as persistent systolic blood pressure >185 mmHg or diastolic blood pressure >110 mmHg)
- (4) Known hemorrhagic tendency (including but not limited to): Baseline platelet count <  $100 \times 10^9/L$ ; Heparin was administered within 48 hours with aPTT  $\geq 35s$ ; on anticoagulant therapy with warfarin and International Normalized Ratio (INR) > 1.7 (Patients with no history or suspected coagulopathy do not need to wait for laboratory results of INR or aPTT prior to enrollment)
- (5) Parenchymal organ surgery and biopsy were performed in the past one month
- (6) Any active bleeding or recent bleeding (gastrointestinal bleeding, urinary bleeding, etc.)

in the past one month

- (7) Undergoing hemodialysis or peritoneal dialysis; Known severe renal insufficiency with glomerular filtration rate <30ml/min or serum creatinine >220mmol/L (2.5mg/dl)
- (8) Brain tumor (with mass effect)
- (9) The expected survival time is less than 1 year (such as comorbidity with malignant tumor, advanced heart or lung disease, etc.)
- (10) Participation in another interventional randomized clinical trials that may confound outcome assessment of the study
- (11) Other circumstances that the investigator considers inappropriate for participation in the study or that may pose significant risks to patients (such as inability to understand and/or follow the study procedures and/or follow up due to mental disorders, cognitive or emotional disorders)

#### **4.2.3 Neuroimaging Exclusion Criteria**

- (1) Midline shift or herniation, mass effect with effacement of the ventricles
- (2) Evidence of acute intracranial hemorrhage
- (3) Acute bilateral strokes or multiple intracranial vessel occlusion

## **5. Imaging protocol**

### **5.1 Baseline imaging**

All researchers were trained in the course of the imaging protocol and the use of RAPID software, and participated in the network training, simulation test and examination of NCCT-ASPECTS before enrollment. The ASPECTS training and test are conducted through the online training system of the trial website (<http://angel-aspect.org>). Those who pass the exam (accuracy rate more than 80%) will obtain the ASPECTS assessment qualification certificate and be qualified for imaging assessment. During imaging screening, researchers in the sub-center with imaging evaluation qualifications and two trained neuroradiologists from the trial team will conduct real-

time online image evaluation of ASPECTS, occlusion site, infarct core volume to ensure the accuracy of the imaging assessment (Figure 2).

- (1) **ASPECTS:** All patients presenting within 24h of symptom onset will undergo a plain CT scan. After the preliminary screening of ASPECTS by trained clinicians in research centers, two dedicated clinicians (insert initials here / names) from the trial team will conduct real-time online evaluation of the prospective patient. When the ASPECTS score reaches a consensus that is between 3 to 5 between the site and central core lab investigators, the patient is then deemed suitable for enrollment into ANGEL-ASPECT. NCCT-ASPECTS will be manually determined independently before RAPID ASPECTS® (version 5.0.4, iSchemaView, CA, USA) assessment.
- (2) **Infarct core volume:** The infarct core volume was automatically evaluated by iSchemaView automated RAPID® software (version 5.0.4, iSchemaView, CA, USA), and the infarction core volume was defined as  $rCBF < 30\%$  based on CTP or  $ADC < 620 \times 10^{-6} \text{ mm}^2/\text{s}$  based on MRI. For patients who present with NCCT-ASPECTS 0-2 within 6 hours from symptom onset, if the infarct core volume is between 70ml and 100ml, then the patient is eligible for enrollment. If the infarct core volume is between 70ml and 100ml in an extend time window (6-24 hours) of stroke onset, the patient is also suitable for inclusion regardless of ASPECTS.
- (3) **Target occlusion vascular:** The occluded arterial was determined by CTA or MRA. Occlusion of the ICA or M1 segment of the MCA is suitable for enrollment. Patients with ipsilateral extracranial internal carotid artery occlusion or stenosis with the above artery occlusion will also be included in this trial. As a tandem lesion can be difficult to distinguish on CTA or MRA, patients with tandem lesion in the EVT group will be confirmed during angiography.

[figure not shown]

Figure 2. Imaging evaluation working flow

## 5.2 Intraoperative and follow-up imaging:

- (1) **Intraoperative imaging:** In the EVT group, preoperative DSA was required to determine the site of vascular occlusion and eTICI score, and postoperative angiography was required to evaluate the eTICI score. It is recommended to conduct NCCT or cone-beam CT immediately after EVT to exclude bleeding.
- (2) **Imaging evaluation of hemorrhage:** The NCCT scan 36 hours ( $\pm 12$  hours) after randomization was taken as the main criterion for the judgment of hemorrhage, and

Heidelberg Bleeding Classification was used to evaluate the classification of hemorrhage.

- (3) **Vascular imaging follow-up:** Vascular imaging (CTA/MRA) was conducted with 36 hours ( $\pm 12$  hours) h after randomization to determine vascular patentability.
- (4) **Evaluation of postoperative infarct volume:** The infarct core volume was determined at 7 days ( $\pm 1$  day) or at discharge assessed with NCCT or at 36 hours ( $\pm 12$  hours) assessed with MRI, and the infarct core volume was determined manually by imaging core lab using validated automated software.

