## **7.4 Secondary safety endpoint**

- (1) All-cause mortality within 90 days ( $\pm 7$  days)
- (2) Any intracranial hemorrhage within 48 hours from randomization (Heidelberg Bleeding Classification)
- (3) Decompressive hemicraniectomy during hospitalization

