 All the enrolled cases should be reviewed with multi-mode imaging 24-48 hours after randomization, and the image evaluation method should be the same as before randomization

 All enrolled cases should be examined by head CT at 7 days (±1 day) after randomization or at discharge which is earlier

 It was only applicable to patients in the standard medical treatment group who did not undergo cervical angiography prior to randomization

 Based on head CT or MRI, determined by the core imaging laboratory

\*MRI sequence includes T1+T2+DWI+ADC+FLAIR sequence

ADC: apparent diffusion coefficient; AE: adverse event; ASPECTS: Alberta stroke program early computed tomography score; CT: computed tomography; CTA: computed tomography angiography; CTP: computed tomography perfusion; EQ-5D-5L: EuroQoL 5-Dimensions 5-Level questionnaire; FLAIR: fluid attenuated inversion recovery; MRA: magnetic resonance angiography; MRI: magnetic resonance imaging; mRS: modified Rankin scale; NIHSS: National Institutes of Health Stroke Scale; PWI: perfusion weighted imaging; SAE: serious adverse event; SWI: susceptibility weighting imaging; TOAST: Trial of ORG 10172 in Acute Stroke Treatment.

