The planned sample size is 502 cases, and two analyses will be conducted when the 90-day follow-up of 1/3 (168 cases) and 2/3 (336 cases) of the total sample size is completed, and the study may be terminated in advance based on clear validity or ineffectiveness. The expected duration of each subject's enrollment is approximately 1 year. Subjects will be followed with assessments at 36 (24-48) hours, hospital discharge (or  $7 \pm 1$  days),  $30 \pm 3$  days,  $90 \pm 7$  days and 12 months  $\pm 14$  days post randomization.

A blinded core laboratory will assess baseline imaging to confirm vessel occlusion

---

and determine ASPECT score, 36 (24-48) hours post-randomization to assess presence of ICH, and to measure core infarct volume and determine angiographical variables such as final reperfusion status and residual stenosis.

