## 5.2 术中及复查影像

- (1) **术中影像**：EVT组患者，术前需要DSA确定血管闭塞部位、eTICI分级，术后造影评估eTICI分级，并确定是否有术中并发症。建议术后即刻复查头CT或行平板CT排除出血。
- (2) **出血的影像判定**：出血判定以48h内的平扫CT为主要判定标准，采用海德堡出血分型评价出血类型并记录。
- (3) **复查血管影像**：随机后36 ( ±12 ) 小时复查血管影像 ( CTA/MRA )，明确血管通畅情况。

- (4) **随访梗死体积判定**：使用经过验证的自动化软件，以随机后7( $\pm$ 1)天/出院NCCT或36( $\pm$ 12)小时MRI评价随访梗死核心体积。

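### A routine CT is recommended straight after EVT only, and the English and Chinese texts set different haemorrhage criteria, so any ICH within 48 h can be detected more often in the EVT arm unless one scan rule is fixed

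*Supplement*

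**What the plan says.** **The extra scan.** Section 5.2(1) of protocol V7.1, on intraoperative imaging in the EVT group, states: "It is recommended to conduct NCCT or cone-beam CT immediately after EVT to exclude bleeding". The Chinese section 5.2(1) says the same: "建议术后即刻复查头CT或行平板CT排除出血". Neither text sets an early scan for BMM patients, and the schedule in section 8.6 lists none.

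**The common scan.** The section 8.6 footnote reads: "All the enrolled cases should be reviewed with multi-mode imaging 24-48 hours after randomization". Section 8.3 allows this imaging to be CT/CTA or MRI/MRA.

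**The haemorrhage criterion.** In English section 5.2(2), the NCCT at 36 (±12) hours "after randomization was taken as the main criterion for the judgment of hemorrhage". Section 5 of the latest SAP has the blinded core lab read images at "36 (24-48) hours post-randomization to assess presence of ICH". Chinese section 5.2(2) reads "出血判定以48h内的平扫CT为主要判定标准", that is, plain CT within 48 hours is the main standard.

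**The endpoints.** The secondary safety endpoint in section 7.4 is "Any intracranial hemorrhage within 48 hours from randomization (Heidelberg Bleeding Classification"). The primary safety endpoint in section 7.3 is sICH over the same window. SAP sections 3 and 13 repeat both without saying which scans count. Under section 5.3, all imaging from onset to discharge is collected for central adjudication.

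**The concern.** Haemorrhage without symptoms is found only when someone looks for it. If one arm is imaged once in the endpoint window and the other is imaged twice, and both scans count, the second arm will show more haemorrhage even when the true rates are equal. Here the extra look belongs to the EVT arm alone, so any distortion overstates the bleeding harm of EVT.

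The 48-hour window starts at randomization and has no lower limit. Section 6 calls for puncture within 1 hour of randomization, so a scan straight after the procedure will normally fall inside the window. The images also reach the core lab. Whether the scan counts therefore depends on the adjudication rule, and the current texts do not give one rule.

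**Working it through.** **1. The rules side by side**

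| Source | Scan that decides haemorrhage | Routine post-EVT plain CT |
|---|---|---|
| English 5.2(2) | NCCT at 24-48 h, main criterion | not named; not excluded, since main is not sole |
| SAP section 5 | core-lab reading at 24-48 h | not named; outside that reading |
| Chinese 5.2(2) | plain CT within 48 h, main criterion | not named; falls within the wording |
| Endpoints (7.3, 7.4; SAP 3, 13) | no scan specified, 0-48 h | inside the window |

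The Chinese text shows no version label in the pages available. Its content matches V7.1 (502 patients, looks at 168 and 336, alpha 0.046), so it is treated as current.

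There is one further gap. A patient whose 36-hour imaging is MRI has no 36-hour NCCT. In the EVT arm, the post-procedure CT may then be the only plain CT within 48 hours.

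**2. The plan's own figure**

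The plan gives no haemorrhage rate, so only the arm size is taken from it. The proportional-odds formula is n per arm = 6(z_α+z_β)² / [(ln OR)²(1−Σp̄³)]. With the stated control distribution, OR 1.73, two-sided 0.046 and power 0.90, it gives 450.3 in total against the stated 452. Then 452/0.9 = 502.2 against 502, or 251 per arm. These figures reproduce, and this point does not affect sample size or power.

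**3. Size for any ICH (illustration on assumed rates)**

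Both models assume equal true rates in the two arms, full uptake of the early scan, and that a positive early scan counts. The chance of a falsely significant EVT excess is Φ{[d − 1.96√(2p̄(1−p̄)/n)] / √[(p₁(1−p₁)+p₂(1−p₂))/n]}. Here d = p₁ − p₂, p̄ is the mean of the two rates and n = 251. The nominal value in that direction is 2.5%.

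*Model A: the early scan adds a positive reading in a fraction x of otherwise negative patients.* EVT rate = p + x(1−p).

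Worked case, p = 25% and x = 10%:
- EVT rate = 0.25 + 0.10 × 0.75 = 0.325
- OR = (0.325/0.675)/(0.25/0.75) = 1.44
- p̄ = 0.2875, so 1.96√(2 × 0.2875 × 0.7125/251) = 0.0792
- denominator = √[(0.2194+0.1875)/251] = 0.0403
- Φ[(0.075−0.0792)/0.0403] = about 46%

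| p | x | EVT rate | OR | Chance of false excess |
|---|---|---|---|---|
| any | 0 (common scan only) | p | 1.00 | 2.5% |
| 25% | 5% | 28.8% | 1.21 | 16% |
| 25% | 10% | 32.5% | 1.44 | 46% |
| 25% | 20% | 40.0% | 2.00 | 95% |
| 15% | 10% | 23.5% | 1.74 | 68% |
| 40% | 10% | 46.0% | 1.28 | 27% |

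The scan is only recommended. At half uptake the effective x is halved: x = 20% then behaves as x = 10%.

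*Model B: a fraction f of true bleeds is visible only early.* EVT shows p, BMM shows p(1−f), and the excess is pf. For p from 20% to 50%:

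| f | Excess (points) | OR | Chance of false excess |
|---|---|---|---|
| 5% | 1.0-2.5 | 1.07-1.11 | 5-8% |
| 10% | 2.0-5.0 | 1.14-1.22 | 8-20% |
| 20% | 4.0-10.0 | 1.31-1.50 | 21-62% |

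**4. Size for sICH**

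Under Model B with assumed rates of 3% to 8% and f up to 20%, the excess is at most 0.08 × 0.20 = 1.6 points, with a false-excess chance of about 10%. The true figure is likely smaller, because Appendix 5 requires deterioration as well as blood on imaging.

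**5. The clock**

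Chinese section 7.3 counts 48 hours from randomization but refers to Appendix 5. Chinese Appendix 5 counts 48 hours from endovascular treatment. In the EVT arm the second window ends later, by the time from randomization to the procedure. In the BMM arm it has no starting point.

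**The case against.** The strongest reply is that the plan largely handles this already. English section 5.2(2) and SAP section 5 both rest the haemorrhage reading on a scan that all patients are due to have. On that reading the extra scan creates no artefact. A clinical event committee reviews safety endpoints under a charter that is not shown, and scan-counting rules may sit there. A flat-panel CT is not plainly a plain CT under the Chinese wording. BMM patients who deteriorate may also be scanned early, so the contrast is not strictly two scans against one. A routine scan in a stable patient cannot by itself make an sICH event. The sizes above rest wholly on assumed rates.

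All of this stands as a limit on size and certainty. It does not remove the gap. The two language versions state different criteria for the same endpoint, no text says that the early scan is left out, and a core-lab reader following the Chinese rule as written would count a post-procedure plain CT.

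A reader might go further and infer that the two versions openly disagree on whether the post-EVT scan counts, or that both haemorrhage endpoints are already biased against EVT. The documents do not support either. Neither text mentions that scan when it sets the criterion, so the difference is read from two time windows, and bias follows only if early findings are counted. Nor does the language version change the direction of any bias: it affects only whether there is an excess, and that excess would always fall on EVT.

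**Conclusion.** The point holds as a gap in the ascertainment rule. Any ICH within 48 hours can be detected more often in the EVT arm, because a routine extra scan exists there alone and the current texts do not agree on which scans decide the endpoint. The effect is zero if only the common 24-48 hour scan is used. Otherwise it ranges from negligible to a material false excess. With 5% to 10% extra positives at an assumed true rate of 25%, the odds ratio is 1.21 to 1.44. The larger figures in the working need 20% extra positives with full uptake and should not be taken as expected values. The exposure of sICH is smaller. The efficacy analysis and the planned sample size are untouched. The separate conflict over the sICH clock in Chinese Appendix 5 is firm, since it rests on text alone.

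**What to change.** 1. Align Chinese section 5.2(2) with English section 5.2(2) and SAP section 5.
2. State in SAP sections 3 and 13 that the main ICH and sICH comparison uses the scheduled 24-48 hour scan, whether CT or MRI, plus any scan triggered by deterioration within 48 hours of randomization, in either arm.
3. Report findings seen only on the routine post-procedure scan separately, and add them in a prespecified sensitivity analysis. This is preferable to counting them only if they persist at 24-48 hours and listing the rest descriptively. Under that rule, true early procedural bleeds would drop out of every formal comparison.
4. Reconcile the clock in Chinese Appendix 5 with the endpoint's clock, so that both arms are counted from the same moment.
5. Carry the same rule into the core-lab and event-committee instructions.

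The cost is wording and one extra sensitivity analysis. No scans are added or removed, and the use of the post-procedure scan in care is unchanged. The small downside is that bleeds seen only early are left out of the main count, though they remain visible in the report.

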### 5.3 Imaging core lab

Tiantan Neuroimaging Center of Excellence (T-NICE) is the imaging core lab of this trial. During the period from onset to discharge, all imaging data (CT, CTA, CTP, MRI, MRA, PWI, DSA) were collected by CRO in DICOM format. T-NICE will conduct quality control. All images will be quality controlled, rendered anonymous and sent to T-NICE for central adjudication. The final results will be reviewed and confirmed by the imaging assessment committee, and then input into the database system.

